### **Primary Outcome Measure**

Change in blinded rater MADRS total score from Baseline to Day 8.

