## 5.5 Outcome Measures

### 5.5.1 Montgomery-Asberg Depression Rating Scale (MADRS)

The MADRS is a 10-item depression rating scale developed in 1979 to be more sensitive to symptom changes induced by antidepressants than were currently available instruments. The MADRS has been used for assessing primary outcomes in registration trials for new pharmacological agents for treating MDD, whether these agents are traditional monoamine modulators or agents with novel mechanisms of action (e.g., esketamine). The MADRS includes questions on the following symptoms 1) Reported sadness, 2) Apparent sadness, 3) Inner tension, 4) Reduced sleep, 5) Reduced appetite, 6) Concentration difficulties, 7) Lassitude, 8) Inability to feel, 9) Pessimistic thoughts, and 10) Suicidal thoughts. Items are scored via a clinical interview that progress from more broadly phrased questions about symptoms to more detailed queries that allow a precise rating of severity. Items are rated to capture the patient's clinical state over the prior week. Each item yields a score of 0 to 6, and higher scores indicate more severe depression. The overall score ranges from 0 to 60.

Various studies have suggested cut scores from  $< 9$  to  $< 12$  as a definition of remission. For the current study, remission will be defined as a score  $\leq 10$ . Response will be defined as  $\geq 50\%$  decrease compared to the last measurement before dosing.

MADRS-S is the self-rating version of MADRS. Apart from item 1 in MADRS, that is deleted from MADRS-S, the two scales are identical.

To reduce the risk of functional unblinding during collection of the primary study outcome measure, MADRS assessments will be conducted by a blinded rater. Raters will be blinded to participant allocation. At any occasion, if a face to face interview is not possible, a non-recorded video interview via an encrypted link will take place.

MADRS ratings will be performed at screening, PET1, day 0, 8, 15, 42, 180 and 365.

At day of dosing, results of MADRS (item 2-10) and MADRS-S before dosing will be used for validation purposes.

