#### **5.5.19 Scale for Psychedelic Intensity Rating (SPIR)**

SPIR is a Likert scale previously applied to measure the psychedelic intensity rating after psilocybin dosing. All subjects are asked to rate psychedelic intensity from 0 = not intense at all, to 10 = very intense. Facilitators will ask the patient to rate psychedelic intensity 90 minutes after dosing.

The participants' verbal response will be coded in the eCRF by a study coordinator at time of rating.

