| MADRS                         | 10            |     | MDs            |                 |                 | MD_P      |    |     | MD1 |   |             | MD1      | MD2                |
| MINI                          | 40            |     | MDs            |                 |                 |           |    |     |     |   |             |          |                    |
| Physical exam                 | 15            |     | MDs            |                 |                 |           |    |     |     |   |             |          |                    |
| Referral ECG                  | 20            |     | MDs            |                 |                 |           |    |     |     |   |             |          |                    |
| Referral blood & urine screen | 20            |     | MDs            |                 |                 |           |    |     |     |   |             |          |                    |
| Confirm eligibility           | 5             |     | MD1            |                 |                 |           |    | MD1 |     |   |             |          |                    |
| Booking LP and PET slot       |               |     | MD1            |                 |                 |           |    |     |     |   |             |          |                    |
| Urine tox and pregnancy       | 5             |     |                |                 |                 | PET_N     |    |     |     |   |             |          | MD_P   |
| MRI1                          | 60            |     |                | x               |                 |           |    |     |     |   |             |          |                    |
| MRI2                          | 90            |     |                |                 |                 |           |    |     |     | x |             |          |                    |
| BSB                           | 5             |     |                |                 |                 | PET_N     |    |     |     |   |             |          | PET_N  |
| PET                           | 120           |     |                |                 |                 | MD_P      |    |     |     |   |             |          | MD_P   |
| PET-spare day                 |               |     |                |                 |                 |           | x  | x   |     |   |             |          |                    |

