| MLQ & SWLS (SRP)           | 1          | MD1    |        |          |          |          |         |          |          |          |          |          | MD1       |
| LEQ (SRP)                  | 3          | MD1    |        |          |          |          |         |          |          |          |          |          | MD1       |
| CGI-S                      | 1          | MD1    |        |          |          |          |         |          |          |          |          |          | MD1       |
| CGI-I                      | 1          | MD1    |        |          |          |          |         |          |          |          |          |          | MD1       |
| Adverse event interview    | 3          | X      |        |          |          |          |         |          |          |          |          |          |           |
| Total duration/day (min)   |            | 26     | 6      | 6        | 6        | 6        | 6       | 6        | 6        | 6        | 6        | 6        | 23        |
| Visit at research site (v) |            | V      |        |          |          |          |         |          |          |          |          |          | V         |

Dur = approximate duration for patient (minutes), W-S = Web screen, S-Day = Screening day, MD1 = Study physician, Medical doctor and study coordinator, MD2=Medical Doctor at MHS, MDs = Screening responsible MD, MD-M = [name]\_P = PET responsible MD, MHS = Mottagningen för hjärnstimulering, MHS\_N = Dedicated nurse from MHS, SRP = Self rating by patient, SRF = Self rated by facilitator, TC = TakeCare, BP = Blood pressure, HR = Heart rate, T-Exp = Treatment Expectation, T-Eval = Treatment Evaluation, PDRF = Post dose release form, PDM = Post dose monitoring, BSB = Blood sampling biomarkers. X = completed by patient. PET2 is done day on 15±7.after LP2 and PET2

Table 1: Schedule of assessments

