#### Role of the Study Physician During Dosing

The on-call Study Physician is responsible for the overall safety of participants, and he/she will oversee the medical management of study participants during the dosing session, as needed.

- Availability during Dosing: The Study Physician will be on-call throughout the duration of the dosing session and the Study Physician or a psychiatry MD will need to be available to be onsite within approximately 5 minutes in the event of an emergency for medical/psychiatric assessment. An MD is responsible for administering rescue medications, should these be warranted.
- End of Dosing Day: The Study Physician or a designated study nurse will assess the participant in-person at the end of the dosing day to determine if he/she is ready to be released from the research site.
- Overnight: In case of need for support during the night the patient will be referred to the emergency ward of the Norra Stockholms Psykiatri (open 24/7/365). The Study Physician will be on-call following participant release and until the following morning when the participant returns for his/her integration session.

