### **9.10 Blinding Related to Delivery of Study Interventions and Collection of Outcome Data**

In order to secure blinding for remaining patients in the study, no patient will receive information of the actual treatment received, with the exception of a serious adverse event, and then at the discretion of the PI or designee.

As with any interventions that produce noticeable psychological effects following administration, blinding psilocybin poses unique challenges.

Prior to start-up, all study site staff will receive extensive training in basic research principles of maintaining the study blind and ensuring only appropriate personnel have access to this information.

Session Facilitators, who will be in the room with participants throughout their dosing sessions, may become functionally unblinded as a result of participants demonstrating changes in behavior and/or speech suggestive of a psychedelic experience, or as a result of participants not demonstrating these types of changes. They will receive written information not to share their thoughts on the outcome of randomization with anyone.

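### The Day 8 MADRS is assigned to a role (study physician and study coordinator) that the protocol does not separate from dosing-day information, so the blinded-rater safeguard is not secured

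*Protocol*

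**What the plan says.** The primary outcome in the synopsis is "Change in blinded rater MADRS total score from Baseline to Day 8". Section 5.5.1 gives the purpose of the blinding: "To reduce the risk of functional unblinding during collection of the primary study outcome measure, MADRS assessments will be conducted by a blinded rater". It adds that raters do not know the allocation and allows an encrypted video interview when a face-to-face one is not possible.

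Table 1 (section 6.3) names who rates. The MADRS goes to MD1 on Days 0, 8, 42 and 365 and to MD2 on Day 15. The CGI follows the same pattern, since section 5.5.4 has the same rater do both. The legend defines the role: "MD1 = Study physician, Medical doctor and study coordinator".

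Both titles in that definition appear in the dosing-day text:

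- **Study coordinator.** Section 5.5.19 has the Facilitators ask for psychedelic intensity (SPIR, 0 to 10) 90 minutes after dosing, and the participant's "verbal response will be coded in the eCRF by a study coordinator at time of rating".
- **Study physician.** Under 9.3.2 the Facilitators report observed symptoms to this physician, who also oversees medical management as needed, is consulted on repeated out-of-range blood pressure or heart rate, and decides on rescue medication. At the close, "The Study Physician or a designated study nurse will assess the participant in-person at the end of the dosing day".

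Section 9.10 says that Facilitators "may become functionally unblinded as a result of participants demonstrating changes in behavior" and speech, or by the absence of such changes. It names no other staff as exposed to this.

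**The concern.** Concealing the randomisation code is not the same as concealing the arm. Psilocybin 25 mg and niacin 100 mg can be told apart from what happens in the session, which is why section 9.10 treats the Facilitators as possibly unblinded. A person who reads the intensity score, hears that a participant had strong perceptual or anxiety symptoms, or assesses release that evening can form a good guess without opening any envelope.

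The MADRS is an interview scale scored by judgement. If the Day 8 rater holds such a guess and expects psilocybin to work, part of the observed difference may be rater expectation. The blinded rater is the protocol's main defence against this, so that person's duties need to be fixed. As written, a site could follow Table 1 and section 9.3 exactly and have the same physician receive dosing-day reports and score the primary endpoint a week later.

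**Working it through.** **Step 1. Compare the passages.**

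| Dosing-day item | Narrative sections | Table 1 |
|---|---|---|
| Presence in the room | 9.3.2 recommends the two Facilitators only; 21.1 also lists the research coordinator, and the PI or physician if required | MHS nurse and Facilitators |
| SPIR | 5.5.19: Facilitators ask, a study coordinator enters the answer | Facilitators |
| Blood pressure, heart rate | 9.3.2: trained staff measure; repeated abnormal values go to the study physician | Facilitators |
| Symptom reports | 9.3.2: Facilitators to study physician | No row |
| Rescue decisions | 9.3.2: study physician | No row |
| Monitoring and release | 9.3.2 and 9.3.3: study physician, or nurse/designee, with the Lead Facilitator | MHS nurse |
| MADRS, Days 0 and 8 | 5.5.1: blinded rater | MD1 |

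MD1's only Day 0 entries in Table 1 are MADRS and CGI-S, and section 5.5.1 refers to that day's MADRS as taken before dosing. So Table 1 gives MD1 no post-dose task on Day 0. The narrative sections attach post-dose information to the same role titles. The adverse event interview on Days 0, 1 and 8 is marked only with an x, so no interviewer is named.

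**Step 2. Look for a rule that separates the rater.** Sections 5.5.1, 5.6.2, 9.3, 9.10 and 21 contain none. No text bars the Day 8 rater from on-call, rescue, release or SPIR duty, and none restricts the rater's view of session data in the eCRF.

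**Step 3. Reproduce the plan's own figure.** Inputs from section 16.1: difference 11, SD 10, two-sided 5% two-group t-test, 80% power. The exact noncentral-t calculation gives power 0.79994 with 14 per arm and 0.828 with 15, so 15 is the smallest number reaching 80%. The stated sample size holds.

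**Step 4. Scale, for illustration only.** The documents give no bias size, so these values are assumed.

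- Standard error of the difference: 10 × √(2/15) = 3.65 points.
- Smallest significant difference with 28 degrees of freedom: 7.48 points.
- Noncentrality with no true effect and bias b: b / 3.65.

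| Assumed bias (MADRS points) | Noncentrality | Two-sided rejection rate |
|---|---|---|
| 0 | 0 | 5% |
| 1 | 0.27 | 5.8% |
| 2 | 0.55 | 8.3% |
| 3 | 0.82 | 12.5% |
| 4 | 1.10 | 18.5% |
| 5 | 1.37 | 26.2% |

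These rates would apply to any trial with 15 per arm and SD 10. They show what a bias would do, not that one is present.

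**The case against.** The strongest reply is that the documents never place the Day 8 rater in the dosing session. Table 1 gives the session, SPIR, vital signs, monitoring and release form to others. The physician duties are on call, as needed or delegable, and another psychiatrist may cover emergencies. The wording on SPIR refers to a coordinator without saying which one; the same title processes forms that Table 1 gives to other staff, and section 21.1 uses a different title. All of this stands. A reader might infer that the primary rater is in fact unblinded; the documents do not support that.

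There are also safeguards. Section 5.5.1 states "MADRS assessments will be conducted by a blinded rater. Raters will be blinded to participant allocation". Section 9.10 provides staff training on the blind and tells Facilitators in writing not to share their views on allocation. Section 5.6.2 puts the MADRS before other outcome assessments at each visit. These help, but Facilitators must still report symptoms to the study physician, and doing the MADRS first on Day 8 does not undo knowledge gained on Day 0. References to a central rater in 7.1.2 and 17.4 have no counterpart in Table 1 and settle nothing.

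A reader might also infer that a positive Day 8 result could not be told apart from rater expectation. That goes too far. The self-rated MADRS-S is collected on Days 1 to 8 and does not pass through the rater. It leaves participant expectancy in place, but it does help isolate rater bias. Nor should the Day 15 rating by MD2 be held against the plan: the only ground would be that MD2 works at the clinic where dosing takes place, and Day 15 is not the primary time point.

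**Conclusion.** The point holds as a gap in the safeguard, not as a demonstrated failure of it. Table 1 and the narrative sections together allow the Day 8 MADRS rater to hold information that points to the arm, and no rule prevents it. The primary endpoint is therefore open to rater expectation bias. How large that bias might be is unknown; the rates of about 8%, 12% and 26% rest entirely on assumed biases of 2, 3 and 5 points and are not estimates. The conclusion also rests on reading MD1 as the same role as the study physician, and possibly the coordinator, of sections 9.3 and 5.5.19. The legend supports this reading but does not prove that one individual does both. It should be fixed; confidence is medium. Rater assignment belongs in the protocol, which already assigns it, so this is not a matter to leave to the analysis plan.

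**What to change.** 1. In Table 1 and section 5.5.1, assign the Day 0 and all post-dose MADRS and CGI ratings to a physician already in the schedule who has no on-call, rescue, release, SPIR or adverse event duty for that participant. MD_P (who rates at PET1) or MDs (who rates at screening) are candidates once confirmed free of such duties; the documents do not establish this. The video link already allowed can be used if needed.
2. Block that rater's eCRF access to SPIR, MEQ, EBI, CEQ, LEQ, dosing-day vital signs and adverse events.
3. Reconcile sections 5.5.19 and 21.1 with Table 1 and section 9.3.2 on who records SPIR and who is in the room.
4. Record the rater's guess of the arm at Day 8. Treat it as descriptive: once response has emerged, a correct guess may reflect improvement rather than unblinding.
5. Report the Day 8 MADRS-S difference beside the Day 8 MADRS difference as a rater-independent check. The secondary endpoints list MADRS-S change only at Day 365 and as a mean over Days 8 to 365, plus response and remission at all time points, so the Day 8 difference needs to be named.

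The cost is a reassignment among existing staff, a change of eCRF rights and one added question. The downside is scheduling around a restricted rater.

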## 7. PARTICIPANT POPULATION

### 7.1 Inclusion and Exclusion Criteria

#### 7.1.1 Inclusion Criteria

Individuals eligible to be randomized in this protocol are those who meet *all* of the following criteria:

1. Are 20 to 65 years old at the time of written informed consent at the In-Person Screening visit
2. Are able to read, speak, and understand Swedish
3. Are able and willing to adhere to study requirements, including attending all study visits, preparatory and follow-up sessions, and completing all study evaluations
4. Are able to swallow capsules
5. Women of childbearing potential (WOCBP) must agree to practice an effective means of birth control throughout the duration of the study, from Screening through the Day 42 assessment
6. Meet ICD-10 criteria for a diagnosis of remitting major depressive disorder and are currently experiencing a major depressive episode of
  - a) at least a 30-day duration at the time of the Screening
  - b) less than 5 years at time of Screening
7. Have sustained moderate-severe depression symptoms at Screening and Baseline, as defined by a Screening MADRS total score  $\geq 22$  and  $\leq 30\%$  and  $\leq 7$  point improvement (i.e. decrease) in MADRS total score from web-screening to screening visit (assuming 3 points on item 1 at web screening).

9. Have an identified support person
  - a. Agree to be driven/accompanied home (or to an otherwise safe destination) by the support person, or another responsible party, following dosing

### 7.1.2 Exclusion Criteria

Individuals not eligible to be randomized in this protocol are those who meet *any* of the following criteria:

1. Women who are pregnant, as indicated by a positive urine pregnancy test at Screening or Baseline. Women who intend to become pregnant during the study or who are currently nursing.
2. Current depressive episode lasting >5 years
2. Unwilling or unable to discontinue formal psychotherapy
3. Ongoing antidepressant drug treatment
4. Have previously during the current episode received the following non-medication treatments:
  - a. deep brain stimulation (DBS)
  - b. vagus nerve stimulation (VNS)
5. Currently receiving electroconvulsive therapy (ECT) or transcranial magnetic stimulation (TMS)
6. Unable or unwilling to discontinue any current medications that are known uridine diphosphate (UDP) or glucuronosyltransferase (UGT) enzyme modulators (eg valproate)
  - o Note: Any prohibited agents must have been stopped at least 5x the elimination half-life of the specific drug at the time of Baseline. See Appendix A for a full list of prohibited medications.
7. Report psychedelic substances use ever
  - o Note: Psychedelic substances include psilocybin, Lysergic acid diethylamide (LSD), mescaline (and natural products containing mescaline including peyote and San Pedro cactus), N,N-Dimethyltryptamine (DMT), natural products containing DMT including ayahuasca and 5-Methoxy-N,N-dimethyltryptamine (5-MeO-DMT), ibogaine, 2C compounds, 3,4-methylenedioxy- methamphetamine (MDMA), methylone or other psychedelics.
8. Have the following cardiovascular conditions:
  - a. coronary artery disease, congenital long QT syndrome (prior diagnosis), cardiac hypertrophy, cardiac ischemia, congestive heart failure, myocardial infarction (prior diagnosis);
  - b. tachycardia (defined as heart rate > 100 beats per minute);
  - c. a clinically significant Screening ECG abnormality (e.g., atrial fibrillation);
    - o Note: A QTcF interval > 450 milliseconds is considered a clinically significant ECG abnormality
  - d. artificial heart valve; or
  - e. any other significant current or history of cardiovascular condition, based on the clinical judgment of study physician, that would make a participant unsuitable for the study
9. At Screening or Baseline have elevated blood pressure as defined as:

- a. Screening blood pressure SBP >135 mmHg or DBP > 85 mmHg on three separate readings; or
  - b. Baseline blood pressure SBP >140 mmHg or DBP > 90 mmHg on three separate readings
10. Have a history of stroke or Transient Ischemic Attack (TIA)
11. Have moderate to severe hepatic impairment, as indexed by a Child-Pugh score  $\geq 7$
12. Have epilepsy
13. Have insulin-dependent diabetes
  - o Note: Participants who are taking oral hypoglycemic agent and have a history of hypoglycemia requiring medical intervention will be excluded
14. Are unable or unwilling to adhere to the following medication requirements:
  - a. Agree to suspend sildenafil (Viagra®), tadalafil, or similar medications at least 72 hours prior to dosing
  - b. If taking any supplement containing >20 mg of niacin, agrees to suspend use for the duration of the study
15. Have a positive urine drug test including Amphetamines, Barbiturates, Buprenorphine, Benzodiazepines, Cocaine, Cannabis, Methamphetamine, MDMA, Methadone, Opiates (Morphine, Oxycodone), Phencyclidine (PCP), and Tetrahydrocannabinol (THC). Exceptions are made for prescribed Benzodiazepines (stable dose for sleep or anxiety).
  - o Note: Benzodiazepine medications for sleep and non-benzodiazepine sleeping medications will be allowed to continue through the study period for participants who have been on a stable dose of such a medicine for at least 6 weeks prior to Screening, as determined during review of concomitant medications
  - o Note: Participants using cannabis, including legal cannabis, for any purposes will be excluded
  - o Note: Participants who are taking prescription maintenance methadone or buprenorphine naloxone will be excluded
  - o Note: Prescription opiates must have been stopped at least 5x the elimination half-life of the specific drug at the time of inclusion, as confirmed with a negative urine drug screen.
16. Nicotine dependence that would disallow an individual to be nicotine free for the 7-10 hours during the dosing period
17. Meet ICD-10 criteria for schizophrenia spectrum or other psychotic disorders, including MDD with psychotic features (except substance/medication-induced or due to another medical condition), or Bipolar I Disorder, Bipolar II Disorder and bipolar disorder NOS.
  - o Note: Participants with any lifetime diagnosis of schizophrenia spectrum or other psychotic disorders will be excluded
18. Meet ICD-10 criteria for antisocial personality disorder
19. Meet ICD-10 criteria for a moderate or severe alcohol or drug use disorder (excluding caffeine)
  - o Note: Participants with a diagnosis of alcohol or drug use disorder within the past 12 months will be excluded
20. Have presence of any psychiatric condition or symptom judged by the PI (or designee) to be a more significant clinical problem than MDD for the participant.
21. Have a first-degree relative with schizophrenia spectrum or other psychotic disorders (except substance/medication-induced or due to another medical condition), or Bipolar I Disorder

22. Have a psychiatric condition judged to be incompatible with establishment of rapport with the Facilitators or safe exposure to psilocybin
23. Report the following suicidal ideation or suicidal thoughts defined as:
  - a. Have a score of  $\geq 5$  on Item 10 (suicidal thoughts) of the central-rater or computer administered MADRS at Screening or Baseline; or
  - b. Have any suicidal ideation or thoughts, in the opinion of the study physician or PI, that presents a serious risk of suicidal or self-injurious behavior at any time prior to randomization
24. Have any suicidal ideation or thoughts, in the opinion of the study physician or PI, that presents a serious risk of suicidal or self-injurious behavior
25. Have any physical or psychological symptom, medication or other relevant finding at Screening or Baseline, based on the clinical judgment of clinical/medical study personnel, that would make a participant unsuitable for the study.
26. Have an allergy or intolerance to any of the materials contained in either drug product
27. Have Hepatitis B, C or HIV
28. Have one or more pathological blood test results as defined in 5.6.3 (as determined by a study physician; with the exception of CRP).

